# SUMMARY

**Rationale:** Postmenopausal women who are sedentary or overweight, have an increased breast cancer risk. It is suggested that these two factors mediate breast cancer risk mainly through sex hormone-related pathways. However, an inactive lifestyle and obesity are highly correlated and it is not clear which is most relevant to risk.

Literature shows that weight loss/ fat loss reduces postmenopausal sex hormone levels, but the question is if there is an additional beneficial effect on hormones of reaching this weight loss by physical activity instead of nutritional interventions.

We, therefore, propose to study the effect of weight loss mainly driven by exercise compared to equivalent weight loss due to calorie restriction only on sex hormones.

**Objective**: To examine the effects of equivalent weight loss with or without exercise training on breast cancer biomarkers in overweight, sedentary postmenopausal women

**Study design:** three-armed, single-blind, randomized controlled intervention study. Two hundred and fifty eligible postmenopausal women will first enter a run-in period of 5 weeks. During this period, all participants get an isocaloric diet adapted to the guidelines for healthy nutrition. After the run-in period, women are randomized into 3 groups: a diet- induced weight loss group (D); a combined exercise- plus diet-induced weight loss group (E); a control group (C) The aim for the women in both weight loss groups is to loose 5-6 kg of body weight. The intervention period lasts for 10-14 weeks. After the weight loss goal is achieved or after a maximum of 14 weeks intervention period, the maintenance period will start. In this period of 2-6 weeks, all participants will be weight-stabilized.

**Study population:** Healthy, overweight and obese (BMI 25-35 kg/m2), sedentary postmenopausal women (aged 50-69).

**Intervention:** Group D will follow an energy-restricted diet (-500 kcal/day). While group E will follow an exercise programme using 350 kCal/day combined with a (less strict) energy restricted diet (-250 kcal/day). The aim of both intervention groups is to loose 5-6 kg of body weight in 10-14 weeks.

**Main study parameters/endpoints:** The primary outcomes are serum estradiol (total, free), estrone, testosterone, sex hormone binding globulin. The secondary measurements include BMI, weight, waist- and hip-circumference, total body fat, abdominal fat (subcutaneous and visceral), fitness and blood pressure.

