## Hypothesis to be tested

We hypothesize that weight loss mainly driven by physical exercise induces a larger decrease in serum estradiol levels compared to equivalent diet-only induced weight loss and control.

To underpin this hypothesis, the association between sex hormones and postmenopausal breast cancer risk (3), the effect of physical activity and obesity on these hormones (4, 5) will be discussed in the next paragraphs.

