## Sample size calculation

Sample size calculations are based on the effect of the interventions on serum estradiol levels. The following comparisons will be made:

1) diet-induced weight loss versus combined exercise- plus diet-induced weight loss

2) diet-induced weight loss versus control

3) combined exercise- plus diet-induced weight loss versus control

The following assumptions are based on the results of the SHAPE study in women with a BMI≥25, the DIANA trial46 and the studies of McTiernan13 and Friedenreich 15:

- Mean log-transformed serum estradiol levels: 2.28 pg/ml
- Log-transformed SD: 0.44 pg/ml
- Change in diet group: -12%; pg/ml
- Change in exercise-weight loss group: -20%: pg/ml
- Power: minimally 80%
- Level of significance: 0.05 for comparison 1 and 0.025 for comparisons 2 and 3 (taking into account multiple testing).
- Drop-out: 5% in all groups
- Non-compliance/contamination: 15%

First, we calculated the sample size for the first comparison, i.e. diet-induced weight loss (n=85) versus exercise-induced weight loss (n=85), since the difference in estradiol levels between these groups is expected to be the smallest (8%). Furthermore, we think a difference of 8% will be of clinical relevance. Based on the estimated sample sizes, we calculated the number of subjects needed in the control group (n=36). The sample size of the control group can be much smaller, since the expected difference with the interventions groups is large (12% and 20%, respectively).

The sample size calculations resulted in the following estimated numbers per group, taking into account drop out and non-compliance:

- - Control group: 45
  - Diet group: 104
  - Combined exercise plus diet group: 104

The accompanying power for the other hormones to demonstrate an 8% difference between the diet and exercise group for is tabulated below:

|  | Diet vs. exercise |
| --- | --- |
| Estrone | 83% |
| Testosterone | 100% |
| SHBG | 96% |

*Abdominal fat measured by MRI*

Based on the study of Ross et al.80 (in their obese study population: mean total visceral fat was 2.3 kg SD 0.8 kg), we calculated that 81 subjects are needed to demonstrate a difference of 0.2 kg visceral fat (Alpha=0.05; Beta=0.20.) between the diet and exercise group.

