# METHODS

## Study parameters/endpoints

### Main study parameter/endpoint

The primary outcome measures are serum sex-hormone levels; estradiol (total, free), estrone, testosterone, sex hormone binding globulin.

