## Analysis

Our primary and secondary endpoints will be changes in sex steroid hormones, body composition and fitness during the study. If sex hormones are non-normally distributed, log transformations will be used for analyses. We will analyse the effects by linear regression analysis. We will compare the effects of the diet group versus the exercise group, the diet versus control, and exercise versus control. The main analysis will be performed according to the intention-to-treat principle, where outcomes for patients are analyzed by assigned treatment, regardless of the level of adherence. As a secondary analysis, adherence will be examined as a potential modifier of the intervention effects.

To explore whether changes in body fat (total, abdominal) mediates intervention effects on sex hormone levels, we examined the change in the measure of association pre- versus post adjustment for changes in body fat (in the linear regression model). If the adjustment attenuates the measure of association, then we consider this to be suggestive of mediation. Furthermore, the main effect of total body fat/ abdominal fat on changes in sex hormone levels will also be evaluated in the linear regression models, adjusting for the intervention assignment. This method is based on a paper of Kraemer et al86 which explains that a mediator must show a change during treatment, must correlate with the treatment assignment, and must have a main or interactive effect on the outcome.

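### The stated split of significance levels does not hold estradiol at 5% when all three arms are equal, and five unranked primary hormones face an estradiol-only hypothesis and sample size

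*Protocol*

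**What the plan says.** In what follows, D is the diet arm, E the exercise-plus-diet arm and C the control arm.

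- **Significance levels.** Section 4.4 numbers three comparisons: (1) D versus E, (2) D versus C, (3) E versus C. It gives "Level of significance: 0.05 for comparison 1 and 0.025 for comparisons 2 and 3 (taking into account multiple testing"). This is the only statement on multiplicity in the protocol. It belongs to a calculation that opens "Sample size calculations are based on the effect of the interventions on serum estradiol levels".
- **Primary outcomes.** Section 5.1.1: "The primary outcome measures are serum sex-hormone levels; estradiol (total, free), estrone, testosterone, sex hormone binding globulin". The Summary agrees: "The primary outcomes are serum estradiol (total, free), estrone, testosterone, sex hormone binding globulin". Neither place ranks the five measures or says how many must be positive.
- **Hypothesis.** Section 1.2 names one hormone. It expects that exercise-driven weight loss "induces a larger decrease in serum estradiol levels compared to equivalent diet-only induced weight loss and control".
- **Analysis.** Section 7.2: "Our primary and secondary endpoints will be changes in sex steroid hormones, body composition and fitness during the study", and then "We will compare the effects of the diet group versus the exercise group, the diet versus control, and exercise versus control". It gives no significance level, order of testing or adjustment.

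**The concern.** Two things do not fit together.

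First, section 4.4 says that multiple testing has been allowed for, yet 0.05 + 0.025 + 0.025 = 0.10. With no stated order and no stated division into families, those levels do not hold the three estradiol comparisons at 5% when no arm differs from another.

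Second, the outcome list is wider than the question. The hypothesis and the sample size concern estradiol, but free estradiol, estrone, testosterone and SHBG carry the same primary status. No rule says which measure answers the trial's question or at what level the other four are tested.

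At stake is how the result will be read. An isolated finding on, say, SHBG could be presented as a primary result with nothing in the protocol to say how much weight it bears.

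**Working it through.** **Inputs.** Levels 0.05, 0.025 and 0.025, and evaluable numbers 85 (D), 85 (E) and 36 (C), all from section 4.4. The number of primary measures, five, is from the Summary and 5.1.1. Three comparisons per measure is from 4.4 and 7.2. Sidedness is not stated.

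**The plan's own figure.** The protocol gives no overall error rate to reproduce. The control-group size does show how the 0.025 was used. With "Mean log-transformed serum estradiol levels: 2.28 pg/ml", log SD 0.44 and the 12% change applied to the log mean, the difference is 0.12 × 2.28 = 0.2736. The standard error for D versus C is 0.44 × √(1/85 + 1/36) = 0.0875, and 0.2736/0.0875 = 3.127. At two-sided 0.025 the power is Φ(3.127 − 2.241) = 81.2%, and 80% needs 35 controls against the stated 36. This supports two-sided levels, which are used below.

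**Estradiol alone, all three arms equal.**
- Upper bound: 0.05 + 0.025 + 0.025 = 0.10.
- If the three tests were independent: 1 − 0.95 × 0.975 × 0.975 = 9.7%.
- With the correlations that shared arms produce: for 85/85/36 the test statistics correlate at 0.39 in absolute value between comparison 1 and either control comparison, and at 0.70 between the two control comparisons. Simulation gives **8.5%**. The result is essentially the same with 104/104/45.

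**Estradiol alone, some arms different.** If any two arms differ, at most one of the three equalities can be true. The chance of a false result is then at most 5% (if D = E) or 2.5% (if one weight-loss arm equals control). The excess exists only when all three arms are equal.

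**Five hormones.** This step assumes that the same three levels are used for every primary measure, which the protocol does not say. It also assumes a common correlation r between hormones, which the documents do not give. Simulation under no effect on any hormone, 400,000 runs, 85/85/36:

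| r | Any of 15 tests | E versus D only (5 tests) |
| --- | --- | --- |
| 0 | 35.9% | 22.6% |
| 0.3 | 33.4% | 20.8% |
| 0.5 | 29.3% | 18.2% |
| 0.7 | 24.4% | 14.9% |
| 0.9 | 16.9% | 10.2% |

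As a check, at r = 0 the last column should equal 1 − 0.95⁵ = 22.6%, and it does. That column is also the relevant one if both weight-loss arms truly differ from control on every hormone, because only E versus D can then be falsely positive.

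**The closed procedure for estradiol.** The overall three-arm test is done at 0.05, and pairs are tested at 0.05 only if it is significant.
- With all arms equal, simulation gives 5.0%.
- Under the planning effects (0.12 × 2.28 for D, 0.20 × 2.28 for E, none for C), the overall test has 99.8% power.
- E versus D: the difference is 0.08 × 2.28 = 0.1824 and the standard error 0.44 × √(2/85) = 0.0675, so power is Φ(2.703 − 1.960) = 77.1%. The overall test leaves this practically unchanged.
- D versus C rises from 81.2% to Φ(3.127 − 1.960) = 87.8%.

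The 77.1% falls short of the planned 80%. That is a separate matter and does not enter the error rates above.

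**The case against.** The strongest defence is that section 4.4 can be read as two families: E versus D, the trial's central question, at 0.05, and the two control comparisons sharing 0.05 as 0.025 each. That would explain the unequal levels, and on that reading estradiol is held at 5% within each family. It is a sensible reading, but the protocol does not state it. Section 1.2 joins the diet-only and control comparisons in one hypothesis, and 7.2 lists all three side by side. Even so, one sentence adopting it would settle the estradiol point.

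The 8.5% also needs all three arms to be equal, against the protocol's premise that weight loss lowers these hormones. This stands, and it limits how much harm the split can do for estradiol.

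A reader might infer that the protocol applies 0.05/0.025/0.025 to all five hormones and so carries a false-positive risk of 24% to 36%. The documents do not support that as a statement of fact. The levels are written inside an estradiol calculation, and no level is given for the other four. The range needs no effect on any hormone and correlations of 0 to 0.7, which are assumed. Its upper end treats total and free estradiol as uncorrelated, which is not credible. Nor does the protocol claim protection across hormones, so it cannot be said to promise that and fail.

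Finally, the five measures do fit the broadly worded primary objective in 2.1, the protocol defines no formal success criterion, and a rule across outcomes is often left to an analysis plan, which is not shown here. All true. What remains is a mismatch within the protocol: one hormone in the hypothesis and sample size, five of equal rank in the outcome list.

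**Conclusion.** The point holds in a limited form and should be fixed.

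- **Firm:** as written, the three levels sum to 0.10. They give about 8.5% for estradiol when all arms are equal, taking two-sided tests and the planned evaluable numbers. The excess over 5% disappears once any two arms differ, or if E versus D is explicitly made its own family.
- **Firm:** five measures are primary without ranking, the hypothesis and sample size rest on estradiol, and the other four have no stated level or rule.
- **Conditional:** if the same levels were used for all five, the chance of at least one false primary result under no effect would be about 17% to 36%, and about 10% to 23% for E versus D alone, for assumed correlations of 0.9 down to 0. This illustrates what the silence could cost; it is not a property that the protocol states.

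**What to change.** Make these changes in the Summary, 4.4, 5.1.1 and 7.2 together. The Summary must be included, since it repeats the list of five and would otherwise contradict the rest.

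1. Name total serum estradiol as the single primary outcome, and list free estradiol, estrone, testosterone and SHBG as secondary.
2. For estradiol, choose one of two rules and state it in 4.4 and 7.2:
   - a closed three-group procedure: overall three-arm test at 0.05, then each pair at 0.05; or
   - E versus D at 0.05 as the only confirmatory comparison, with both control comparisons secondary.

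The cost is mainly wording. Four hormones lose the primary label, and under the closed procedure the pairwise tests depend on an overall test. The basis given for the control-group size (level 0.025) must be restated. Under the closed procedure the planned 36 evaluable controls remain sufficient: on the protocol's own planning inputs, read as above, power for D versus C is about 88% instead of 81%. No participants need be added on this account. The change should be made before any unblinded results are seen.

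### The 15% non-compliance allowance in section 4.4 fits loss of subjects, but the intention-to-treat main analysis keeps non-compliers in, so 80% power is not shown for the protocol's own effect size

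*Protocol*

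**What the plan says.** Protocol section 4.4 (Sample size calculation) bases the trial's size on serum estradiol. Its inputs are "Mean log-transformed serum estradiol levels: 2.28 pg/ml", "Log-transformed SD: 0.44 pg/ml", "Change in diet group: -12%; pg/ml" and a 20% fall in the exercise-plus-diet arm. The targets are "Power: minimally 80"% and "Level of significance: 0.05 for comparison 1 and 0.025 for comparisons 2 and 3". Two allowances stand on separate lines: 5% drop-out and "Non-compliance/contamination: 15"%.

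The section first gives 85 per weight-loss arm and 36 controls. It then gives 104, 104 and 45, introduced by "The sample size calculations resulted in the following estimated numbers per group, taking into account drop out and non-compliance". It shows no inflation formula and does not say how a non-compliant woman's estradiol is expected to behave.

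Section 7.2 (Analysis) makes the main analysis intention-to-treat, "where outcomes for patients are analyzed by assigned treatment, regardless of the level of adherence". Adherence comes in only as a possible effect modifier in a secondary analysis.

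**The concern.** Drop-out and non-compliance act on power in different ways. A woman without an end-of-study sample reduces the number analysed, so dividing n by 0.95 is right for 5% drop-out. A non-compliant woman who gives blood is still analysed in her assigned arm under section 7.2. She costs no observation but pulls the arm means together. If the difference shrinks to 0.85 of plan, n must be divided by 0.85 squared to keep the same power. One division by 0.85 is right only for an analysis that leaves non-compliers out.

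The 80% is the protocol's justification for its size. The comparison most exposed is exercise plus diet versus diet, which carries the hypothesis in section 1.2 and has the smallest planned difference. If its power is lower than stated, a null result would be read as stronger evidence of no added exercise effect than it is.

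**Working it through.** **1. Which inflation was used?** Inputs from section 4.4: 85 to 104, 36 to 45, drop-out 5%, non-compliance 15%.

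- Stated factors: 104/85 = 1.22 and 45/36 = 1.25.
- 15% as lost subjects: 1/(0.95 × 0.85) = 1.24. This gives 85 × 1.238 = 105.3 and 36 × 1.238 = 44.6. The control figure rounds up to 45; the other is within about one subject of 104.
- 15% as dilution: 1/(0.95 × 0.85²) = 1.46. This gives 123.8 (124) and 52.4 (53), far from both printed figures.

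A plain 20% deduction also fits the controls (36/0.80 = 45) and gives 85/0.80 = 106.25 for the other arms. It too treats non-compliers as lost.

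**2. What difference lies behind 85 per arm?** Two-sided alpha 0.05 is assumed (the protocol does not state sidedness), with n = 2 × [0.44 × (1.960 + 0.842)/δ]².

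- Taking 8% of the log mean, δ = 0.08 × 2.28 = 0.1824, gives n = 91.3, i.e. 92. With 85 per arm, power is 77.1%.
- The difference at which 85 per arm gives exactly 80% is δ = 0.44 × 2.802 × √(2/85) = 0.189. Rounded to 0.19, the formula gives 84.2, i.e. also 85.

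So 85 is slightly short of its own stated inputs, which is a separate matter. Both differences are carried forward.

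**3. Exercise plus diet versus diet under intention-to-treat.** Analysed per arm: 104 × 0.95 = 98.8. Power = Φ(f × δ/0.44 × √(98.8/2) − 1.960), where f is the share of the planned difference that remains.

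| How non-compliers respond | f | δ = 0.1824 | δ = 0.189 |
| --- | --- | --- | --- |
| No dilution | 1 | 83.0% | 85.6% |
| Keep half the effect, both arms | 0.925 | 76.9% | 79.8% |
| No effect, both arms | 0.85 | 69.7% | 72.8% |
| 15% in each arm respond like the other arm | 0.70 | 53.2% | 56.1% |

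At δ = 0.19 the last column becomes 85.9%, 80.2%, 73.2% and 56.5%.

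The factor 0.85 arises in two simple ways. If 15% in each arm get no effect, the changes are 0.85 × 20% = 17.0% and 0.85 × 12% = 10.2%, a difference of 6.8%. If 15% of the exercise arm respond only like diet, they are 0.85 × 20% + 0.15 × 12% = 18.8% against 12%, again 6.8%. In both cases 6.8/8 = 0.85.

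**4. Comparisons with control.** Two-sided alpha 0.025 (z = 2.241); analysed controls 45 × 0.95 = 42.75; standard error 0.44 × √(1/98.8 + 1/42.75) = 0.0805.

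- Diet: δ = 0.12 × 2.28 = 0.2736. Undiluted power is 87.6%; at f = 0.85 it is 74.1%.
- Exercise plus diet: δ = 0.20 × 2.28 = 0.456. At f = 0.85 power is still above 99%.

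**5. Size that would keep 80% at f = 0.85.** From the printed base, 85/(0.95 × 0.85²) = 124 per arm. From δ = 0.1824, the diluted comparison needs 127 analysed, i.e. 127/0.95 = 134 per arm.

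**The case against.** Several objections deserve weight.

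**The method is inferred.** No formula is printed, and the lost-subject factor gives 105.3 from 85, not exactly 104. A reader might back-solve a base of 84 (104 × 0.8075 = 83.98) and treat the formula as established, but 84 appears nowhere in the protocol. What stands is weaker and sufficient: both printed steps lie close to a lost-subject factor and far from a dilution factor.

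**Non-compliers may really be lost.** Section 5.4 lets the investigator withdraw a woman who does not comply with the intervention. If she then gave no final sample, she would be lost n. That withdrawal is discretionary, and leaving such women out would conflict with section 7.2. It does not rescue the calculation.

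**The planned effects may already contain non-adherence.** Section 4.4 derives them from earlier trials, and the introduction quotes several of those results for whole arms. If so, a further 0.85 double-counts and power is 83–86%. The separate 15% line suggests full-compliance effects, but the text does not settle it.

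**The response of non-compliers is unknown.** Non-response confined to the exercise arm would give about 44–47%; confined to the diet arm, about 95%. Contamination, which the protocol names in the same line, narrows the difference between the two weight-loss arms.

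**The SD may not be that of the analysed outcome.** Section 7.2 analyses changes, while 0.44 stands beside the mean log level. If 0.44 is the SD of levels, the SD of change is 0.44 × √(2(1 − r)), where r is the baseline-to-end correlation, which is not given. At f = 0.85, assumed values of r = 0.4, 0.6 and 0.7 give 62–65%, 79–82% and 89–91%.

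These points limit the figure. They do not make one division by 0.85 an allowance suited to intention-to-treat.

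**Conclusion.** The point holds. The 15% appears to have been allowed for as loss of subjects, while the declared main analysis keeps those women in. The claim of at least 80% power after allowing for non-compliance is therefore not supported on the protocol's own effect size.

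The size is conditional on three assumptions: −12% and −20% are full-compliance effects, 0.44 is the SD of the analysed outcome, and the net difference falls to 0.85 of plan. Exercise plus diet versus diet then has about 73% power and diet versus control about 74%; exercise plus diet versus control is not materially affected.

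A reader might infer more, and the documents do not support it:

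- That dilution alone takes power from 80% to 70%. The 70% uses δ = 0.1824, where 85 per arm gives only 77% before any non-compliance. The like-for-like figure is 73%.
- That 70–73% is an established property of the design. It moves with the assumed response of non-compliers: about 77–80% if they keep half the effect, about 53–57% with full cross-over.
- That about 124 per arm would restore 80% in every case. It does so near δ = 0.189; at 0.1824 it gives 77%, and 134 are needed.

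All of these figures use the effect size as the protocol used it. Taking 8% of a log mean is a separate problem. Read as falls of 20% and 12% on the original scale, the log difference is ln(0.88/0.80) = 0.095, and 98.8 per arm gives about 33% power before dilution and 25% at f = 0.85.

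**What to change.** In section 4.4:

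1. Count only the 5% drop-out as loss of n.
2. State how non-compliant or contaminated women are assumed to respond, and whether the planned changes are full-compliance effects.
3. Apply the 15% as a reduction of the expected difference, with 0.85 as the base case.
4. Restate the power at 104/104/45 as a range under those assumptions, and name the SD used and the outcome it belongs to.

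Do this in the same recalculation that corrects the log-scale difference and the base number, so that the protocol carries one consistent power statement. The cost is a recalculation and a few sentences. Recruitment need not change if the power is restated rather than restored.

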## Secondary objectives

To examine the effects on body(fat) composition and whether this mediates potential changes in endogenous sex hormones

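### Section 4.4's 81 subjects for a 0.2 kg visceral-fat difference does not follow from the only SD given (0.8 kg), which needs about 252 per arm; the SD of the analysed change is not stated

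*Protocol*

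**What the plan says.** Section 4.4 bases the trial's size on serum estradiol: 85 women in each weight-loss arm, raised to 104 for drop-out and non-compliance. A separate paragraph then deals with abdominal fat by MRI. It takes its variability from a cited exercise trial ("in their obese study population: mean total visceral fat was 2.3 kg SD 0.8 kg") and concludes: "we calculated that 81 subjects are needed to demonstrate a difference of 0.2 kg visceral fat (Alpha=0.05; Beta=0.20.) between the diet and exercise group".

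The paragraph does not say whether 81 is per arm or the total of the two arms, or whether the test is one- or two-sided. It gives no SD of change and no correlation between baseline and follow-up.

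Section 5.1.2 lists visceral fat among the secondary endpoints. Section 7.2 defines the endpoints as changes during the study, analysed by linear regression. Section 2.2 sets the secondary objective: "To examine the effects on body(fat) composition and whether this mediates potential changes in endogenous sex hormones".

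**The concern.** The sentence on visceral fat gives every input of a two-group sample size calculation, and its answer is about a third of what those inputs require if 81 is per arm, or about a sixth if it is the total. A reader cannot tell whether the number is wrong or whether it rests on an SD that was left out.

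This matters because abdominal fat is part of the trial's explanation of how exercise might act. Sections 1.1 and 1.6 ask whether exercise-driven weight loss removes more total and abdominal fat and thereby gives better hormone effects. Section 7.2 requires a mediator to be correlated with treatment assignment. A reader who trusts 80% power for 0.2 kg may take a null diet-versus-exercise result as evidence against the fat pathway, when the trial may not have been able to see a difference of that size.

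**Working it through.** **Inputs.** All from section 4.4: difference 0.2 kg, SD 0.8 kg, alpha 0.05, power 80% (beta 0.20), stated result 81. Two-sided testing is my assumption, with one-sided also tried. The correlation r between baseline and follow-up visceral fat is not in the protocol, so a range is shown.

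**1. Trying to reproduce 81.** The standardised difference is 0.2/0.8 = 0.25.

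- Two groups, two-sided: n per arm = 2 × (1.96 + 0.8416)² × 0.8²/0.2² = 2 × 7.849 × 16 = 251.2, so 252 per arm (504 in total).
- Two groups, one-sided: 2 × (1.645 + 0.8416)² × 16 = 197.8, so 198 per arm.
- One group or paired, two-sided: 7.849 × 16 = 125.6, so 126.
- One group or paired, one-sided: 98.9, so 99.

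None gives 81, per arm or in total.

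**2. What 81 would deliver if 0.8 kg is the SD of the analysed variable.** Two-sided power = Φ(0.2/(0.8 × √(2/n)) − 1.96). Detectable difference at 80% power = 2.8016 × 0.8 × √(2/n).

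| Women per arm | Power for 0.2 kg | Detectable difference at 80% power |
|---|---|---|
| 40.5 (81 in total) | 20% | 0.50 kg |
| 81 | 36% | 0.35 kg |
| 85 (before inflation) | 37% | 0.34 kg |
| 99 (104 less 5% drop-out) | 42% | 0.32 kg |

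**3. What SD would make 81 right.** SD = 0.2 × √(n/2)/2.8016.

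- 81 per arm: 0.2 × √40.5/2.8016 = 0.454 kg. For change scores, SD = 0.8 × √(2(1 − r)), so r = 1 − (0.454/0.8)²/2 = 0.84. For baseline-adjusted regression (ANCOVA), SD = 0.8 × √(1 − r²), so r = √(1 − (0.454/0.8)²) = 0.82.
- 81 in total (40.5 per arm): 0.321 kg, r about 0.92 by either route.

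**4. Power for 0.2 kg over a range of assumed correlations**, with 0.8 kg as the SD of level.

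| r (assumed) | 81 per arm: change score / ANCOVA | 99 per arm: change score / ANCOVA |
|---|---|---|
| 0.5 | 36% / 45% | 42% / 53% |
| 0.7 | 54% / 61% | 62% / 69% |
| 0.8 | 71% / 76% | 79% / 83% |
| 0.85 | 83% / 86% | 90% / 92% |

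At r = 0.5 the SD of a change score equals 0.8 kg. Above that it is smaller; below it, larger. The ANCOVA SD never exceeds 0.8 kg.

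**The case against.** The strongest reply is that 0.8 kg describes how women in the cited study differed in their level of visceral fat, whereas this trial analyses change. An SD of change near 0.45 kg would make 81 per arm correct, and it may have been used without being written down. That stands. It means a missing input is as consistent with the text as a wrong number. It does not make the printed calculation right, because the one SD offered does not lead to the result.

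A reader might infer that the real power for visceral fat is 20% to 36%. The protocol does not support that, for two reasons. The range holds only if 0.8 kg is the SD of the analysed variable. It also belongs to 81 women, per arm or in total, whereas 104 per weight-loss arm are planned. With 99 remaining after drop-out, the table in step 4 runs from 42% to 92% for r between 0.5 and 0.85, so the planned arms may or may not reach 80%. For the same reason it would go too far to say that the trial cannot detect 0.2 kg.

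A third reply is that visceral fat is one secondary endpoint among several, that enrolment rests on estradiol, and that the mediation analysis is exploratory, covers total as well as abdominal fat, and looks mainly at attenuation after adjustment. This also stands and lowers the severity. It does not remove the point: the protocol makes a specific power claim about this endpoint, and its inputs and result disagree.

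**Conclusion.** The point holds in conditional form. Section 4.4's figure of 81 cannot be obtained from the difference, SD, alpha and beta printed with it; those need about 252 per arm. If 0.8 kg applies to the analysed variable, and testing is two-sided, 80% power is available only for about 0.32 to 0.35 kg with 81 to 99 per arm. For 81 per arm to be right, the SD must be about 0.45 kg, that is, a correlation of about 0.84 (change score) or 0.82 (ANCOVA), and the protocol states neither. The actual power for 0.2 kg therefore cannot be determined from this document.

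Severity is moderate. The trial's size and primary endpoints are unaffected, but the claim bears on how a null visceral-fat result would be read against the secondary objective.

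**What to change.** Replace the visceral-fat sentence in section 4.4 with a calculation from a sourced SD of change, or a sourced baseline to follow-up correlation, matched to the regression model that will be used. State whether the number is per arm or total and whether the test is one- or two-sided, and give the power or detectable difference for the planned arms after drop-out. The SD should come from data and not be chosen because it returns 81.

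If no such source exists, withdraw the claim of 81 subjects for 0.2 kg. Report instead that, on an SD of 0.8 kg, 85 per arm give 80% power for about 0.34 kg, and label this a conservative figure. It is conservative for a baseline-adjusted analysis, and for change scores if the correlation is at least 0.5; say which is assumed.

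The cost is a sentence or two of protocol text. No additional participants or scans are needed.
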